### Economic evaluation

The economic evaluation in our study is being performed from a societal perspective, which implies that all costs and outcomes are taken into account if possible. The economic evaluation will be a combination of a cost-effectiveness and a cost-utility analysis. The primary outcome measure for the cost-effectiveness analysis will be the percentage of people sustaining a fall during one year of follow-up. As mentioned above, falls are recorded by means of a calendar. Within the cost-utility analysis, the effects are measured in terms of generic health-related quality of life descriptions, measured according to the standard Dutch version of the EuroQol (EQ 5-D) [20] in self-administered questionnaires at baseline and after four and twelve months. A direct value for every state of health is generated using the social tariff [24], which involves an algorithm for interpolating EuroQol results to population utilities.

We will assess programme costs, healthcare costs and patient and family costs. All costs are measured by means of a cost diary [25], in which patients continuously record volumes of health care utilisation during the twelve-month follow-up period. Subjects are asked to report their cost diary relating to the previous month during the same monthly telephone interview in which they report falls from the calendar. The volume of each category we measure will be multiplied by the cost price of each category. Cost prices are presented in Euros. Health care costs are estimated according to the Dutch guideline for cost analysis in health care research [26]. Where such guidelines are not available for a specific category, real costs or tariffs are used to estimate costs.

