### Intervention programme

To adapt the programme developed by Close et al. [5] to the Dutch situation, and to make improvements based on recent insights, we performed a review of the literature, convened a consensus meeting and tested the adapted version in a pilot study (n = 36). Based on this process, we made some improvements to Close et al.'s programme.

The final programme includes a medical and occupational therapy assessment resulting in recommendations. The medical assessment consists of an examination performed by a geriatrician, a geriatric nurse and a rehabilitation physician to identify and address risk factors for falling. The examination includes a comprehensive general examination, but in addition focussed on a more detailed assessment of visual acuity, stereoscopic vision, mobility, balance, cognition, affect, use of medication and examination of feet and footwear. Recommendations or indications for referral resulting from this examination are sent to the patient's GP. After the medical assessments, an occupational therapist visits the patients to identify possible risk factors for falling in the home environment. The therapist makes recommendations regarding adaptations to the home environment, assistive devices, home care and behavioural change. Recommendations by the occupational therapist are sent directly to the subjects themselves and to their GPs. As stated before, the intervention period is scheduled to last for a maximum of 3.5 months after the baseline measurement.

An important addition to Close et al.'s protocol [5] is the collaboration with a rehabilitation physician (physiatrist) in the medical part of the intervention. In addition to the screening by a geriatrician, our programme also involves screening by a rehabilitation physician who examines the subjects' feet and the shoes which the subjects wore at the time of the fall. Details of the process of adaptation and the contents of the intervention programme will be published elsewhere.

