### Process evaluation

The process evaluation involves assessing the extent to which the intervention programme is performed according to protocol, the nature of the recommendations made to the participants, participants' compliance with these recommendations and the opinions of participants, physicians and therapists about the intervention programme and recommendations. Data on these topics are collected using the following methods: structured registration forms for the medical and occupational parts of the intervention programme; self-administered evaluation forms filled in by the participants after the medical intervention; interviews by telephone with the participants six weeks or longer after the recommendations are sent and interviews with all participating physicians and therapists at the end of the intervention period.

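### Programme costs are to be measured with the patients' own cost diary, which may under-record or misclassify them; the delivery records already being collected are a better source

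*Protocol article*

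**What the plan says.** The Economic evaluation section of the protocol article sets out three categories: "We will assess programme costs, healthcare costs and patient and family costs". The source follows at once: "All costs are measured by means of a cost diary", described as one "in which patients continuously record volumes of health care utilisation during the twelve-month follow-up period". Patients report the diary in the monthly telephone interview. On valuation the section says "The volume of each category we measure will be multiplied by the cost price of each category".

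The Process evaluation section lists a different source of information on programme delivery: "structured registration forms for the medical and occupational parts of the intervention programme". No section links these forms to the costing.

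The Analysis section puts the between-group difference in mean costs in the numerator of the incremental cost-effectiveness and cost-utility ratios.

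**The concern.** The rule covers all three categories, but the instrument suits only two of them. A patient diary is a natural source for other health care and for patient and family costs. Programme cost is the cost of delivering an intervention, and the trial team's own delivery records are closer to it than a patient's recollection.

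Only the intervention arm incurs this cost. If diary reporting of ordinary care is incomplete to a similar degree in both arms, part of the error offsets in the difference. Incomplete recording of programme contacts has no counterpart in the control arm. It is a systematic error, so a larger sample does not reduce it. The planned sensitivity analysis, which works with the confidence limits of cost and effect variables, would not reveal volumes that were never recorded.

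**Working it through.** The documents state no programme cost, unit price or expected cost difference, so there is no plan figure to reproduce. The check compares the sections and then scales the possible error.

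**1. What the diary can see.** The Intervention programme section describes two kinds of input.
- Contacts the patient attends: "The medical assessment consists of an examination performed by a geriatrician, a geriatric nurse and a rehabilitation physician", followed by an occupational therapist's home visit. A patient can enter these.
- Work behind the contacts: "Recommendations or indications for referral resulting from this examination are sent to the patient's GP", and the therapist's advice goes to both patient and GP. A patient largely cannot see this work. It reaches the cost total only if the price per contact includes it, and the article does not say whether it does.

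**2. How a contact is classified.** No section says whether a programme contact written in the diary counts as programme cost or as health care cost. The call-centre operators are kept unaware of allocation (Design section), so asking them to label contacts as programme or ordinary care could reveal the arm. A contact labelled as ordinary care still enters total cost once. The total is wrong only to the extent that the ordinary price differs from the programme price.

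**3. Missing reports.** The Sample size calculation section expects about 25% dropout: 123 / (1 − 0.25) = 164 per group, so 164 − 123 = 41 per group. Where a diary report is missing, programme resources already used are missing with it. The programme is scheduled to finish within 3.5 months of baseline, so people who leave later may already have reported their programme contacts. For loss through dropout, 25% is therefore a ceiling. It would be reached only if everyone who dropped out had received the programme, had reported none of it, and was counted as zero.

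**4. Passage into the ratio.** Let C be the true programme cost per intervention participant and u the share of it not recorded.
- Error in incremental cost = −u × C
- Planning difference in the proportion who fall = 0.52 − 0.32 = 0.20 (Sample size calculation section)
- Error in cost per faller avoided = −u × C / 0.20 = −5 × u × C

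Each euro missed per intervention participant therefore lowers cost per faller avoided by 1 / 0.20 = 5 euros.

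**5. Illustration.** Both C and u are assumptions, chosen only to show scale.

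| Assumed C (EUR) | u = 0.25 | u = 0.50 |
|---|---|---|
| 300 | −375 | −750 |
| 600 | −750 | −1,500 |
| 1,000 | −1,250 | −2,500 |

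Entries are errors in EUR per faller avoided. The documents give no planning difference in utility, so the cost-utility ratio cannot be scaled in the same way.

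**The case against.** The strongest reply has three parts.

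- **The diary records volumes, not costs.** A patient need only enter the contact, and the price can carry the preparation, reporting and letters behind it. The section also allows for categories without a guideline price: "Where such guidelines are not available for a specific category, real costs or tariffs are used to estimate costs". This stands in part. A price that includes overhead could cover the hidden work, so it is not shown that reporting time would be lost. But the provision concerns prices. It supplies no volume for a contact that was never recorded.
- **The programme contacts are few, early and reported monthly.** Patients may well record most of them, and analysts could try to identify them by discipline and date. This also stands in part: the documents do not show that under-recording will occur or how large it would be. It does not help where the report itself is missing.
- **A journal article condenses the full protocol.** A costing method left unstated would be no finding. Here the article states a method that covers all costs and gives no exception. Nothing bars use of the registration forms for costing, but the written rule points to another source.

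Two stronger conclusions are tempting, and the documents support neither. A reader might infer that programme visits would be counted twice. With a single source each visit is entered and priced once; double counting would need a second source added without a rule to remove overlap, and the article describes no second source. A reader might also infer that programme cost is the main cost difference between the arms. It is the category that differs by design, but no cost sizes are given, and differences in other care could be larger.

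**Conclusion.** The point holds as a badly fitted measurement rule. As written, programme costs rest on patients' recording and on completed monthly calls. That may under-record or misclassify them, and the resulting error would not cancel between arms. Unrecorded contacts would make the programme look cheaper than it is, by 5 euros per faller avoided for each euro missed per intervention participant. This rate assumes that the planning difference of 0.20 is realised; a smaller effect would give a larger rate. The total cannot be stated, because it depends on a programme cost and a recording rate that the documents do not give. The rule should be changed because a better source is already being collected.

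**What to change.** Replace the single-source sentence with a split rule:

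1. Take programme volumes for every participant allocated to the intervention from the structured registration forms for the medical and occupational parts. Value them at a cost price that includes reporting time.
2. Use the cost diary only for other health care and for patient and family costs. Care that follows from the programme's recommendations stays in the diary.
3. Before pricing, remove diary entries that match a registered programme contact by date and discipline. This step is needed because the registration forms become a second source, and without it the change would itself create double counting.

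The cost is small. The forms are already part of the process evaluation, so the change is a revised rule plus the matching work. If the forms do not record staff time, an estimate of time per contact for each discipline is also needed.

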### Process evaluation

The process evaluation involves assessing the extent to which the intervention programme is performed according to protocol, the nature of the recommendations made to the participants, participants' compliance with these recommendations and the opinions of participants, physicians and therapists about the intervention programme and recommendations. Data on these topics are collected using the following methods: structured registration forms for the medical and occupational parts of the intervention programme; self-administered evaluation forms filled in by the participants after the medical intervention; interviews by telephone with the participants six weeks or longer after the recommendations are sent and interviews with all participating physicians and therapists at the end of the intervention period.

### Analysis

Data will be primarily analysed according to the intention-to-treat principle, i.e., including all participants with valid data, regardless of whether they received or did not receive the intervention. Subsequently, the results of the intention-to-treat analysis will be compared with the results of an on-treatment analysis, to assess whether protocol deviations have caused bias. Participants with documented deviations from the study protocol (i.e., participants in the intervention group who did not receive the entire intervention or participants in either the intervention or the control group with incomplete follow-up data) will be excluded from this on-treatment analysis.

Comparability between the intervention and control groups will be assessed at baseline to check for differences between the two groups. Outcome at four and twelve months will be compared between the intervention and control groups by both univariate and multivariate techniques. We will use multivariate analysis to adjust for possible differences in baseline scores and background variables between the intervention and control groups. Dropouts and losses-to-follow up will be described.

The economic evaluation will involve calculating cost-effectiveness and cost-utility ratios. The additional costs and additional benefits of the intervention programme compared with usual care will be examined by calculating incremental cost-effectiveness and cost-utility ratios. These incremental ratios represent the difference in mean costs between the intervention and usual care groups in the numerator and the difference in mean effects in the denominator[27].

Since the recruitment period is only 14 months, and the follow-up period is also relatively short (12 months), it is unlikely that there will be substantial differences between costs made by and for patients who started in the first part of the recruitment period and those who started in the last part. Therefore, discounting of costs is not required. Finally, a sensitivity analysis will be done to assess the generalisability of the assumptions made in the costing process. This sensitivity analysis, which involves calculating the upper and lower limits of the confidence interval of cost and effect variables, will allow us to explore and quantify the uncertainty not related to sampling variations.

The process evaluation will mainly be analysed by means of descriptive techniques.

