### Sample size calculation

Sample size calculations were based on the expected effects of the intervention on the main outcome measure, the percentage of people sustaining a fall during one year of follow-up. The study by Close et al. [5] found that the percentage of persons who sustained a recurrent fall was 52% in the usual care group and 32% in the intervention group. If we want to detect the same reduction in the percentage of persons sustaining a recurrent fall in our study, with a power (1-beta) of 90% and alpha of 0.05, we need 123 patients in each group (a total of 246). Based on the experiences of Close et al. and our own experiences in trials among elderly people in the Netherlands [14], we expect a dropout rate of about 25% during the one-year follow-up period. This means that about 164 persons per group (a total of 328) have to be included in the study. The inclusion period was 14 months.

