### Effect evaluation

The primary outcome measures of the effect evaluation are number of falls and daily functioning. Number of falls is subdivided into three separate measures: the percentage of elderly people sustaining a fall during the one-year follow-up period, recurrent falls during follow-up (i.e., the percentage of elderly people sustaining two or more falls), and injurious falls during follow-up (the percentage of elderly people receiving medical care after a fall). Falls are recorded continuously by means of a fall calendar during the twelve-month follow-up period. Subjects are called monthly to report their falls as recorded on the fall calendar relating to the previous month.

We decided to measure daily functioning by means of the Frenchai Activity Index (FAI) [15], in contrast to Close et al. [5], who used the Barthel Index. Our reason for choosing this instrument was that the FAI has proved to be suitable for the general population of elderly people [14] and has at least two advantages over the Barthel Index. One is that the Barthel Index shows a ceiling effect when applied to elderly people who have sustained a fall [5]. The other is that most activities of daily living (ADL) scales, like the Barthel Index, do not refer to complex activities like housekeeping, recreation, hobbies and social interaction. These so-called instrumental abilities (IADL) may affect the quality of life considerably, and the FAI focuses primarily on these IADL abilities [15]. The FAI is measured by means of self-administered questionnaires at baseline and after four and twelve months.

Our secondary outcome measures are: recuperation from the fall, health complaints, perceived health measured by means of the first two items of the RAND-36 [16], ADL and IADL disability measured by means of the GARS (Groningen Activity Restriction Scale) [17], mental health measured by means of the HADS (Hospital Anxiety and Depression Scale) [18,19] and quality of life measured by means of the European Quality of Life instrument (EuroQol) [20]. The secondary outcome measures are assessed by means of self-administered questionnaires at four and twelve months.

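### The analysis labelled intention-to-treat covers only participants with valid data, and the one-year fall percentages have no defined value for someone who leaves early without a fall

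*Protocol article*

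**What the plan says.** In the protocol article, Analysis, the primary analysis follows the "intention-to-treat principle, i.e., including all participants with valid data, regardless of whether they received or did not receive the intervention". What makes data valid is not defined. On people who leave, the same section says only: "Dropouts and losses-to-follow up will be described". It also plans an on-treatment analysis, which excludes participants in either arm whose follow-up is incomplete.

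Under Sample size calculation the trial is sized on "the main outcome measure, the percentage of people sustaining a fall during one year of follow-up". In the study being replicated, the percentage with a recurrent fall "was 52% in the usual care group and 32% in the intervention group". The section adds: "we expect a dropout rate of about 25% during the one-year follow-up period".

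Under Effect evaluation all three falls outcomes are percentages over the year: any fall, two or more falls, and a fall needing medical care. The data are finer than that: "Falls are recorded continuously by means of a fall calendar during the twelve-month follow-up period", and each month is reported by telephone. Progress of the study gives 166 participants in the intervention group and 167 in the control group.

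**The concern.** The definition keeps one half of intention-to-treat, since people are analysed whether or not they received the intervention. It replaces the other half, everyone randomised, with those who have valid data. That would matter little with near-complete follow-up, but the article plans for a loss of a quarter.

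A one-year percentage treats leavers unevenly. A person who falls in month 2 and leaves in month 5 is a known faller. A person who leaves in month 5 without a fall is neither a known faller nor a known non-faller. The same applies to someone who leaves with one fall (for the recurrent outcome) or with no medically treated fall (for the injurious outcome). The wording leaves open how these people count, and different answers move the result in different directions. If the choice is made after the data are seen, the main result depends on it.

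The planned comparison with an on-treatment analysis does not help. That analysis removes incomplete follow-up altogether, so it cannot show what losing those participants does to the result.

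**Working it through.** **Inputs.** Fall risks 52% and 32%, power 90%, alpha 0.05 and dropout 25% (Sample size calculation); 166 and 167 randomised (Progress of the study). *Assumed, not in the article:* constant hazard of a first fall; dropout unrelated to falling and uniform over the year; the unequal dropout rates in step 4.

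**1. The plan's own figure.** Two-sided, unpooled: (1.960 + 1.282)² × (0.52×0.48 + 0.32×0.68) / 0.20² = 10.51 × 0.4672 / 0.04 ≈ 122.7, so 123 per group. Then 123 / 0.75 = 164. Both reproduce, and the sample size is not in question. Expected dropouts: 0.25 × 333 ≈ 83.

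**2. Chance that a dropout has a recorded fall.** With λ = −ln(1 − p), the probability of a fall before a uniform dropout time is f = 1 − p/λ.
- p = 0.52: λ = 0.734, f = 0.292.
- p = 0.32: λ = 0.386, f = 0.170.

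**3. Three readings of valid data, dropout d = 25% in each arm.**

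| Reading | Formula | Control | Intervention | Difference (points) |
|---|---|---|---|---|
| (a) Completers only | p | 52.0% | 32.0% | 20.0 |
| (b) Completers plus dropouts with a recorded fall | [(1−d)p + df] / [(1−d) + df] | 0.4629/0.8229 = 56.3% | 0.2826/0.7926 = 35.7% | 20.6 |
| (c) Everyone, non-falling dropouts counted as non-fallers | (1−d)p + df | 46.3% | 28.3% | 18.0 |

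Reading (a) discards about 83 × 6 ≈ 500 person-months, which is 0.125/0.875 = 14% of observed time.

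**4. No true effect (52% in both arms).** With equal dropout all three readings give zero. With more dropout in the intervention arm:

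| Dropout, intervention/control (assumed) | (a) | (b) intervention reads | (c) intervention reads |
|---|---|---|---|
| 30%/20% | 0 | 57.3% vs 55.3%, 2.1 points higher | 45.1% vs 47.4%, 2.3 points lower |
| 35%/15% | 0 | 58.5% vs 54.3%, 4.2 points higher | 44.0% vs 48.6%, 4.6 points lower |

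**5. If dropout is related to falling.** Reading (a) then loses its protection. Suppose the 25% who leave the intervention arm really have a risk of 52%. The true intervention risk is 0.75×32 + 0.25×52 = 37%, a difference of 15 points, while completers still show 20. The extreme bounds with 25% missing per arm are 0.75×52 − (0.75×32 + 25) = −10 and (0.75×52 + 25) − 0.75×32 = +40 points.

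**6. What the partial follow-up is worth.** First falls using all follow-up: 167×0.463 + 166×0.283 = 77.3 + 46.9 ≈ 124. Among completers: 0.75×(167×0.52 + 166×0.32) ≈ 105. The hazard ratio is 0.386/0.734 = 0.525, so |ln HR| = 0.644.
- All follow-up, variance 1/77.3 + 1/46.9: 0.644/0.185 − 1.96 = 1.52, power 93.5%.
- All follow-up, Schoenfeld: 0.644×√(124.2/4) − 1.96 = 1.63, power 94.8%.
- Completers, two proportions at 125 per arm: 90.5% (unpooled) or 89.8% (pooled).

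**The case against.** **The readings are not forced.** The article says only that participants with valid data are included and that arms are compared by univariate and multivariate techniques. Survival or person-time methods are not ruled out. This stands: readings (a) to (c) show what the wording allows, not what the trial will do.

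**Completers only fits the text least well.** Incomplete follow-up is a reason for exclusion from the separate on-treatment set, which implies that some partial follow-up stays in the primary set. A reader might infer that a quarter of the sample will be thrown away, or point to the division by 0.75 as proof. The documents do not support that; the inflation is a planning allowance, not an analysis rule.

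**Unequal dropout is conjecture.** The article gives one rate, about 25%. Refusing the intervention visits does not remove anyone from the primary set, and outcome calls run alike in both arms through a call centre unaware of allocation. This stands, so the 4–5 points are an illustration at a wide split. A reader might infer that the main result is certainly biased. That does not follow either: with equal, unrelated dropout the difference barely moves.

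**Censoring has the same weakness.** Kaplan-Meier also assumes that dropout is unrelated to falling, and a completers-only check cannot test this. This stands and shapes the fix.

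**A design article leaves missing-data detail to fuller documents.** True of imputation and model choice, which are not raised here. But the article itself states this definition of intention-to-treat, so the definition can be judged.

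**Conclusion.** The point holds in a limited form and should be fixed. The set the article calls intention-to-treat is an available-data set, and with about 83 of 333 expected to leave, the one-year fall percentages are not defined for early leavers without a fall.

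The certain harm is ambiguity: the permitted readings put the control risk anywhere from 46% to 56% against a true 52%, and two of them err in opposite directions when dropout is unequal. Bias in the comparison is only possible. At the article's own 25% in both arms it is +0.6 or −2.0 points on a 20-point difference, and nil under the null. It reaches about 2 to 5 points only with assumed unequal dropout, and is nil for completers only whenever dropout is unrelated to falling. All these sizes rest on the constant-hazard and uniform-dropout assumptions. The power gained from the partial follow-up, from about 90% to about 93–95%, is useful but modest.

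**What to change.** - **Analysis set.** Define the primary set as all 333 randomised, by allocated arm, and reserve the intention-to-treat label for it.
- **Falls.** Estimate the 12-month risk of any fall, of a first injurious fall and of a second fall by Kaplan-Meier, censoring at the last completed monthly call. Report the risk difference between arms. The planned percentages survive as 12-month risks, and each person counts for as long as they were observed.
- **Daily functioning.** Analyse the activity index with a mixed model over baseline, 4 and 12 months. The baseline questionnaire preceded randomisation, so every randomised participant with a baseline score contributes.
- **Sensitivity.** Add an analysis for informative dropout, for example best/worst-case or delta-adjusted imputation, and report the completers-only percentages beside it.

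The cost is analysis wording; falls and contacts are already recorded month by month. The drawback is that the headline becomes a Kaplan-Meier risk rather than a simple percentage, so it is slightly less direct to set against the study being replicated. The completers-only result helps there.

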## Design and methods

### Design

Figure 1 shows the design of the study presented, which is a two-group randomised controlled trial. At this stage, the randomisation process has already been completed. Randomisation was achieved by means of computerised alternative allocation and performed by an external agency. Randomisation took place after completion of a self-administered baseline questionnaire. People allocated to the control group received usual healthcare, while people in the intervention group underwent a medical and occupational therapy assessment. The intervention period is scheduled to last for a maximum of 3.5 months after the baseline measurement. After baseline measurement, all subjects are followed for a twelve-month period. During this follow-up period, falls and healthcare utilisation are measured continuously. Subjects are contacted monthly by telephone for an interview about their falls and healthcare utilisation. In addition, self-administered questionnaires are sent to the subjects after four and twelve months.

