### Usual care in the Netherlands

People in the control group receive usual care. At present, no guidelines exist for the systematic assessment of the underlying causes of an injurious fall presented at an A&E department or GP cooperative in the Netherlands. In usual care, medical risks and other risk factors such as environmental hazards in the home and patients' risk behaviour are not systematically registered and addressed by hospital physicians, specialists or general practitioners. Moreover, no systematic attention is currently being paid to the specific consequences of an injurious fall for the daily functioning of individual patients in their unique situation. We placed no restrictions on co-interventions.

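### The on-treatment comparison cannot show whether protocol deviations biased the intention-to-treat result, because it drops non-receivers from the intervention arm only and can create selection bias in either direction

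*Protocol article*

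**What the plan says.** The Analysis section of the protocol article defines the primary analysis as intention-to-treat, "including all participants with valid data, regardless of whether they received or did not receive the intervention". The result is then to be "compared with the results of an on-treatment analysis, to assess whether protocol deviations have caused bias".

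Two groups are excluded from the on-treatment analysis:

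- "participants in the intervention group who did not receive the entire intervention"
- "participants in either the intervention or the control group with incomplete follow-up data"

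Three other statements bear on how this works:

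- Usual care in the Netherlands: "People in the control group receive usual care".
- Design, on the programme: "The intervention period is scheduled to last for a maximum of 3.5 months after the baseline measurement".
- Design, on follow-up: "After baseline measurement, all subjects are followed for a twelve-month period", with falls recorded continuously.

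The Analysis section also plans covariate adjustment: "We will use multivariate analysis to adjust for possible differences in baseline scores and background variables between the intervention and control groups".

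**The concern.** The first exclusion can only remove people from the intervention arm, since a usual-care participant has no programme to miss. What remains is a group selected after randomisation, set against controls who were not selected in that way.

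Selection related to the outcome is plausible here. Frailer people may be less able to attend. In addition, a fall or an admission in the first months counts as an outcome and can also stop someone completing the assessment or the home visit.

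A difference between the two analyses therefore mixes two things: dilution of the effect by non-receipt, and selection of who is left. The comparison has no means of separating them. The plan nevertheless uses the contrast that randomisation no longer protects to judge the one that it does protect. If the replication gave a null intention-to-treat result and a more favourable on-treatment one, the stated purpose would invite the explanation that deviations had masked a benefit, which the comparison could not support.

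**Working it through.** **The plan's own figures.** The article gives 52% versus 32% with recurrent falls, 90% power, alpha 0.05 and 123 per group. With the unpooled normal formula, two-sided:

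(1.960 + 1.282)² × (0.52×0.48 + 0.32×0.68) / 0.20² = 10.51 × 0.4672 / 0.04 = 122.7, so 123. Then 123 / 0.75 = 164.

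Both figures reproduce, and this point does not concern them. They supply the 52% risk, the planned 20-point effect and the expected number of completers. With 166 and 167 allocated and 25% dropout, that is about 125 per arm (0.75 × 166 = 124.5; 0.75 × 167 = 125.3).

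**Inputs the article does not give.** These are f, the share of intervention completers who did not receive the whole programme, and r, their fall risk relative to receivers. Both are assumed below and shown over a range.

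**Formula.** With no true effect, both arms have risk 0.52. In the intervention arm 0.52 = (1−f)·p_R + f·r·p_R, so the receivers' risk is p_R = 0.52 / [(1−f) + f·r]. The on-treatment difference (intervention minus control) is p_R − 0.52, although the true difference is zero. Equivalently, its size is f times the risk gap between non-receivers and receivers.

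| f | r = 1.25 | r = 1.5 |
|---|---|---|
| 7% | 0.52/1.0175 = 0.511; −0.9 points | 0.52/1.035 = 0.502; −1.8 points |
| 20% | 0.52/1.05 = 0.495; −2.5 points | 0.52/1.10 = 0.473; −4.7 points |
| 30% | 0.52/1.075 = 0.484; −3.6 points | 0.52/1.15 = 0.452; −6.8 points |
| 40% | 0.52/1.10 = 0.473; −4.7 points | 0.52/1.20 = 0.433; −8.7 points |

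**Where 7% comes from.** Non-receivers and dropouts may be largely the same people. If 30% of the 166 allocated (about 50) are non-receivers and all 41 or so dropouts are among them, 50 − 41 = 9 remain among 125 completers, or 7%. This is the extreme overlap case.

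**Other directions.** With r = 1 the difference is zero. If non-receivers' risk is 20 points lower than receivers' and f is 10-30%, the difference is 0.10 × 20 = 2 to 0.30 × 20 = 6 points against the programme.

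**Comparison with an allocation-based estimate.** If controls do not receive the programme, the complier-average effect is the intention-to-treat risk difference divided by the proportion of the intervention arm who received it. With no true effect the numerator has expectation zero whatever f and r are, so the estimator is centred on no effect.

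**Second exclusion.** Incomplete follow-up is removed from both arms. It is a separate selection after allocation and not part of the one-arm asymmetry. An intention-to-treat set restricted to valid data already shares part of it.

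**The case against.** A fair defence has four parts.

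- **The bias is conditional.** A reader might infer that the exclusion necessarily creates bias, or bias in the programme's favour. The article does not support that. It gives neither the rate of non-receipt nor its relation to fall risk. Fitter people who see no need for the programme could be the ones who skip it. This stands.
- **The plan adjusts.** The background variables listed under Effect evaluation include age, falls in the previous year and medication, all measured at baseline. Adjustment may reduce the selection, and the figures above are unadjusted. But it cannot be assumed to remove the selection, and baseline covariates cannot account for a fall or admission that occurs after baseline and interrupts the programme.
- **Intention-to-treat stays primary.** A reader might infer that the trial's false-positive rate is inflated or its main estimate compromised. Neither follows: the article states no rule for claiming efficacy from the on-treatment result and does not say that this result will be tested.
- **A complier-average estimate is not the only remedy.** Its test of no effect is essentially that of intention-to-treat, and it needs assumptions of its own. The Usual care section places no restrictions on co-interventions, so controls' lack of access to the programme is an assumption and not a stated fact. This stands too.

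None of these arguments rescues the stated purpose. Whichever way the bias runs, and even if it is small, the comparison cannot tell dilution from selection.

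**Conclusion.** The point holds in a limited form. The article fixes both the rule and its purpose, so this is not detail left to an unseen analysis plan. The rule removes non-receivers from one arm after randomisation, during a period that overlaps the outcome window, and a gap between the two analyses is therefore not evidence that intention-to-treat is biased.

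Under the stated assumptions the spurious difference runs from about −0.9 to −8.7 points. That is roughly 5% to 43% of the planned 20-point effect (0.9/20 and 8.7/20). It is zero if non-receipt is unrelated to fall risk and changes sign if non-receivers are at lower risk. Its true size and direction cannot be known from the article. The fault lies in how a secondary comparison would be interpreted, and the primary estimate is untouched. It should be corrected before results are read.

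**What to change.** 1. Delete the stated purpose of using the on-treatment comparison to detect bias from protocol deviations, and label the on-treatment result descriptive. This is the minimum correction.
2. Base any estimate of the effect of receiving the programme on a complier-average causal effect, with allocation as the instrument and all participants with valid data kept. Give a bootstrap interval.
3. Define receipt in advance from the structured registration forms described under Process evaluation. If the definition is looser than completing every part (for example, attending at least the medical assessment), say why. Counting partial receivers as treated makes it more credible that allocation acts only through receipt.
4. State the assumptions: allocation affects falls only through receipt, and controls do not receive the programme.

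The cost is a change to the analysis wording. No new data are needed and the sample size does not change. The downside is a wider interval than intention-to-treat, with essentially the same test of no effect.
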